## Statistical analysis plan

A hypothesis test will be conducted using Mixed-Model Analysis of Variance of Repeated Measures (RM-ANOVA), followed by Bonferroni corrections to examine differences between groups. In this analysis, pre-test and post-test evaluations will act as the within-subject factor (repeated measures), while the comparison between the experimental and control groups will serve as the between-subject factor. Partial eta squared will be used to quantify effect size, assuming variables meet the assumptions of homoscedasticity and normality for parametric tests; otherwise, non-parametric tests will be employed.

To analyze the relationship between participants' performance and various sociodemographic variables acting as potential confounders, multivariate linear regression analysis will be conducted for numerical variables, and logistic regression analysis will be applied for categorical variables.

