**Table utbl0001:** 

Subject Area:	• Cognitive sciences
More specific subject area:	• Children's Cognitive Development
Name of your method:	Randomized controlled trial to evaluate the effect of a cognitive training program
Protocol name:	Effects of computer-based cognitive training vs. paper-and-pencil-based training on the cognitive development of typically developing children: Protocol for a randomized controlled trial.
Reagents/tools:	• Computer-based cognitive training • Paper-and-pencil cognitive training
Experimental design:	A randomized controlled trial with intra-subject and inter-subject evaluations will feature two parallel groups: an experimental group and an active control group. Pre-test and post-test measures will be conducted. Participants will consist of two third-grade classes, aged 7 to 10 years (*N* = 58). Random allocation will be employed. Primary measures will include neuropsychological tests to assess executive functions (cognitive flexibility, working memory, inhibitory control, planning, and attention). The experimental group will undergo computer-based cognitive training, while the control group will undergo paper-and-pencil cognitive training. The intervention will take place at the educational institution, twice a week in 40-minute sessions, spanning 8 weeks with a total of 16 sessions. Evaluators responsible for pre-test and post-test measurements will be blinded to the allocation. Researchers in charge of the intervention will be blinded to the evaluation results.
Trial registration:	The study was registered in the Office of Research and Scientific Development at University of Tolima under code 50,119.
Ethics:	The randomized controlled trial complies with the ethical parameters defined by the Helsinki Declaration [1], as well as the norms for health research established by the Colombian Ministry of Health [2] in Resolution 8430. Parents and guardians of the children who agree to participate will sign informed consent forms. This randomized controlled trial has been approved by the bioethics committee of University of Tolima, as documented in minutes No. 10 of December 13, 2022.

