## Specific objectives and hypotheses

The current randomized controlled trial (RCT) aims to evaluate the effect of computerized cognitive training on the executive functions of third-grade neurotypical children, aged 7 to 10 years, compared to paper-and-pencil cognitive training. In response to these research objectives, the following working hypotheses have been formulated:-Null Hypothesis (H_0_): There are no significant differences in executive functions between children receiving computerized cognitive training and those receiving paper-and-pencil cognitive training.-Alternative Hypothesis 1 (H_1_): It is expected that the group of children receiving computerized cognitive training will show greater improvements in their executive functions compared to those receiving paper-and-pencil cognitive training.-Alternative Hypothesis 2 (H_2_): It is expected that the group of children receiving paper-and-pencil cognitive training will show greater improvements in their executive functions compared to those receiving computerized cognitive training.

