## Outcome measures

The executive functions of the children will be assessed using neuropsychological tests that have established validity and reliability for this population and within the context of such studies. The selection of tests for this protocol was based on recommendations from Robledo et al. [39]).•**Planning**

To assess planning, the Tower of London test has been selected. This cognitive task, originally designed by Tim Shallice in 1982 and later constructed and validated by Culbertson & Zillmer [41], evaluates executive functions, particularly planning and problem-solving. The test requires participants to move a series of colored disks between three poles to achieve a specific configuration using the fewest possible moves. The task includes constraints such as limits on the number of disks that can be moved at once and rules prohibiting larger disks from being placed on top of smaller ones.•**Working memory**

Since working memory comprises various components, different measures were selected to assess each process. For verbal-auditory working memory, the Digit Span subtest of the WISC-V (Wechsler Intelligence Scale for Children, Fifth Edition) was chosen. This subtest includes two main parts: Forward Digit Span and Backward Digit Span [42]. In the Forward Digit Span task, the evaluator reads a series of numbers aloud at a steady pace, and the child repeats them in the same order they were presented. The length of the number sequences progressively increases from shorter to longer sequences. In the Backward Digit Span task, the procedure is similar, but the child is required to repeat the numbers in reverse order.

Spatial working memory will be assessed using the Corsi Block-Tapping Task, a component of the Wechsler Memory Scale III battery [43]. This task involves a set of identical blocks arranged in fixed positions with irregular distances between them [44]. During the task, the evaluator taps the blocks in a specific sequence, which the participant must then reproduce by tapping the blocks in the same order they were presented. The sequence length gradually increases throughout the task. Similar to the Digit Span test, the Corsi Block-Tapping Task includes two parts: in the first part, the participant taps the blocks in the same order as presented, and in the second part, they tap the blocks in reverse order.

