For visual working memory, the Visual Span subtest of the WISC-V test battery [42] will be used. In this task, the child is shown a series of images in a specific order. Subsequently, a larger group of images is presented, and the child must identify the images and their sequence from the initial presentation. The number of images progressively increases throughout the task.•**Inhibitory control and cognitive flexibility**

To assess inhibitory control and cognitive flexibility, the classic Stroop test task was selected [45]. The Stroop Test evaluates interference control, mental flexibility, and attentional management. The test is based on the interference phenomenon, which occurs when processing one feature of a stimulus interferes with processing another. In the first part of the task, the subject is given a list of color words (blue, red, green) written in black ink and must read them in order. Next, a list of stimuli consisting of three letters 'X' printed in different colors is presented, and the subject must name the color of the ink. Finally, a list of color words (blue, red, green) printed in various colors is shown, and the subject must indicate the color of the ink without reading the word. The subject has 45 s to complete each list.

Another measure to assess cognitive flexibility will be the Wisconsin Card Sorting Test (WCST), a neuropsychological assessment tool that evaluates planning ability, cognitive flexibility, abstract reasoning, and problem-solving. A shortened version of 48 cards has been validated for use in children [46]. In this test, the subject must sort a series of cards that vary in color, shape, and number of figures. The goal is for the participant to identify a sorting rule that is not explicitly stated and that changes throughout the test. The challenge lies in the individual's ability to detect changes in the sorting rule and adapt to them flexibly.•**Attention**

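### Eight primary instruments serve one null hypothesis with no primary score or decision rule, and the stated Bonferroni step does not, as worded, cover the outcomes; either the 5% error rate or the 80% power in Table 1 fails

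*Protocol article*

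**What the plan says.** **Primary outcomes.** The Experimental design row of the Specifications table states: "Primary measures will include neuropsychological tests to assess executive functions (cognitive flexibility, working memory, inhibitory control, planning, and attention" (the list closes there). No score is singled out.

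**Instruments.** Outcome measures names eight: Tower of London, Digit Span, Corsi blocks, Visual Span, Stroop, Wisconsin Card Sorting, d2 and Trail Making. Three are given in two parts. For Digit Span: "This subtest includes two main parts: Forward Digit Span and Backward Digit Span". For Corsi: "Similar to the Digit Span test, the Corsi Block-Tapping Task includes two parts". Trail Making has parts A and B. The article does not say whether parts are analysed separately.

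**Hypotheses.** Specific objectives and hypotheses sets one null: "There are no significant differences in executive functions between children receiving computerized cognitive training" and those on paper-and-pencil training. H1 favours the computerized arm and H2 the paper-and-pencil arm.

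**Analysis.** The Statistical analysis plan section specifies a mixed repeated-measures ANOVA (time within subjects, group between subjects), "followed by Bonferroni corrections to examine differences between groups". It does not give the family or the number of tests.

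**Sample size.** Table 1 gives effect size 0.75, alpha 0.05, power 0.8, two groups, two measures, 29 per group and 58 in total.

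**Attention.** The Specifications table lists it within executive functions. The section on computerized and paper-and-pencil programs sets it apart as a basic process. The hypotheses do not mention it.

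**The concern.** One global hypothesis is to be judged on many outcomes, and nothing says how many must differ, or which. Because H1 and H2 point in opposite directions, one test could support H1 while another supports H2.

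The named correction is attached to group differences. With two groups each outcome has a single between-group contrast, so a correction over groups has almost nothing to correct. The multiplicity lies across outcomes, and the text does not mention it there.

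At stake is the trial's only confirmatory claim. Its false-positive rate is either uncontrolled or, if a correction across outcomes was intended, bought with power that the sample size does not provide.

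**Working it through.** **1. Reproduce the sample size.** Inputs from Table 1: effect size 0.75 (metric not stated, read as Cohen's d), alpha 0.05, power 0.80. I take the test as two-sided because both directions are alternatives.

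- Normal approximation: n per group = 2(1.960 + 0.842)² / 0.75² = 2 × 7.85 / 0.5625 = 27.9, so 28.
- Two-sample t-test: 28.90, so 29 per group and N = 58. Power at 29 per group is 0.801.
- One-sided t-test: 22.7, so 23 per group.
- Repeated-measures ANOVA with f = 0.75 or 0.375 and correlation 0.5 between measures: total N from 8 to 44.

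Of the readings tried, 58 comes only from one two-sided t-test at unadjusted alpha 0.05.

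**2. Count the tests.** Five domains; eight instruments; eleven scores if Digit Span, Corsi and Trail Making each yield two (8 + 3 = 11). The first two counts are stated in the article. The third is inferred from how the tests are administered.

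**3. Error if there is no correction across outcomes.** For k independent tests at 0.05, the chance of at least one false difference in either direction is 1 − 0.95^k. For correlated tests it was simulated under the global null with equal correlations. The document gives no correlations, so these are assumptions.

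| Tests | r = 0 | r = 0.3 | r = 0.5 | r = 0.7 |
|---|---|---|---|---|
| 5 | 23% | 21% | 18% | 15% |
| 8 | 34% | 30% | 25% | 19% |
| 11 | 43% | 37% | 31% | 22% |

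A t-based simulation with 29 per group agreed within about one point (for example 26.0% for 8 tests at r = 0.5). If attention is outside H0, six instruments remain: 1 − 0.95^6 = 26.5% if independent.

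**4. A generous reading of the Bonferroni step.** Suppose groups are compared at both pre-test and post-test, each at 0.025. The post-test error over independent outcomes is still 1 − 0.975^8 = 18%, or 1 − 0.975^11 = 24%.

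**5. Power if Bonferroni was meant across outcomes.** Family-wise error is then at most 5%. Power for a given outcome at d = 0.75 with 29 per group (two-sided t-test):

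| Tests | Alpha per test | Power | n per group for 80% |
|---|---|---|---|
| 1 | 0.05 | 80% | 29 |
| 5 | 0.05/5 = 0.01 | 58% | 44 |
| 8 | 0.05/8 = 0.00625 | 51% | 48 |
| 11 | 0.05/11 = 0.00455 | 47% | 51 |

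**The case against.** The best counter-argument is that the Bonferroni sentence is ambiguous. It speaks of corrections in the plural and states no family. Because a correction over two groups is nearly empty, the authors may have meant one across outcomes, which would hold the error at 5% or less. This is also a condensed article, and a fuller plan may define the family and the scored variables. That stands as far as it goes: the text does not prove that outcomes go uncorrected. It does not rescue the plan, because the sample size in the same article allows for no such correction. Under that reading the power statement fails instead.

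A reader might make several stronger inferences that the documents do not support:

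- **That a false-positive rate of some 30-40% is established.** The protocol never says that one significant score rejects H0. Without a rule the error rate is undefined, and the figures in step 3 are conditional on that rule. They also fall as correlation rises.
- **That there are eleven primary endpoints.** Forward and backward, or A and B, describe administration. The Specifications table lists domains, and five tests give 23% at most.
- **That the figures apply to a false claim for one pre-named mode.** They count either direction. For a named mode and independent tests they are about 18% (8) or 24% (11).

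The powers in step 5 are for one given outcome. The chance of at least one significant result is higher if several outcomes truly differ, and Holm is somewhat more powerful than Bonferroni in that case. Table 1, however, rests on a single test.

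Table 2 promises publication whatever the result. That limits selective publication but does not control multiplicity.

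**Conclusion.** The point holds in conditional form. The whole battery is primary for one H0, no score or rule decides it, and the only correction named does not on its plain wording reach the outcomes.

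- **No correction across outcomes, any hit rejects H0:** the chance of at least one false difference in either direction is 34% for eight independent instruments. The range is about 15-43% over 5 to 11 tests and assumed correlations of 0 to 0.7. Even the lowest figure is about three times the nominal 5%.
- **Bonferroni across outcomes:** power per outcome is about 47-58%, not 80%, with 0.75 read as Cohen's d.

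Table 1's error rate and power therefore cannot both hold for a multi-outcome primary claim tested outcome by outcome. The unclear place of attention adds to this, because it leaves the family that decides H0 unfixed. This should be settled before unblinding, since it bears on the main conclusion.

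**What to change.** Before unblinding:

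1. Name one primary endpoint that decides H0, H1 and H2. One option is an executive-function composite: the mean of baseline-standardised test scores, all oriented so that higher is better. Test the between-group difference in change two-sided at 0.05, with the sign deciding between H1 and H2. This keeps the single-test basis of Table 1, provided the sponsor states that the 0.75 refers to the composite. A single key test would serve the same purpose.
2. State whether attention is inside or outside the primary family, and align the Specifications table, the background section and the hypotheses.
3. Make the individual tests secondary, with Holm adjustment across every score actually tested. Adjusting over eight instruments is not enough if their parts are analysed separately.
4. Replace the between-group Bonferroni step with these rules.

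If no composite or single key test is used, apply Holm across all primary scores and restate the power in Table 1. As a guide, 80% power per outcome under Bonferroni needs 44, 48 or 51 per group for 5, 8 or 11 tests.

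The preferred route costs only a change of wording and needs no new data. The small downside is that single-test results become secondary.

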## Protocol design

The study is designed as a randomized controlled trial with intra-subject and inter-subject evaluations, employing a crossover design involving two simultaneous groups: an experimental group undergoing computerized cognitive training and an active control group undergoing traditional paper-and-pencil cognitive training. Two measures will be administered—one before the intervention (pre-test) and another after the intervention (post-test). Subsequently, following the post-test, the groups will switch interventions. The clinical trial protocol adheres to the CONSORT guidelines [38]. Fig. 1 illustrates the experimental design scheme.

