## Sample size calculation

A projected estimate was conducted using G-Power to establish parameters for sample size calculation (see Table 1), based on previous studies that reported moderate to large effect sizes in similar research [39]. This estimation suggests a group size of 29 children, resulting in a total sample size of 58 children.

**Table 1 tbl0001:** Parameters for group size calculation.

Parameter	Value
Effect size	0,75
α confidence level	0,05
Sample power	0,8
Number of groups	2
Number of measures	2
Total sample size	*N* = 58
Sample size per group	*N* = 29

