**Experimental group**

The experimental group will participate in computerized cognitive training. The intervention will take place in the computer lab of the participating educational institution. Each session will last 40 min, with a frequency of two times per week, for a duration of eight weeks, totaling 16 sessions.

For the development of the intervention, the digital platform 'NeuronUP' has been selected as the digital environment for cognitive stimulation and executive function training (see Fig. 2). NeuronUP is a cognitive rehabilitation and stimulation platform hosted on a cloud system, allowing access from any device via a web login [50]. In a systematic review by Guerrero & García [28], NeuronUP was analyzed and compared with other neuropsychological rehabilitation platforms. The authors found that NeuronUP had strengths in adaptability, flexibility, evidence of effectiveness, data management, and treatment, receiving a rating of 7.14 out of 10.

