The researchers reviewed the available activities, and after a pilot exercise, 54 activities are selected and distributed across the 16 sessions. Each session consists of 8 activities, each programmed for 5 min, for a total of 40 min per session. Although each digital activity contributes to the training of various cognitive functions, activities with an emphasis on one cognitive process are selected for each session. Accordingly, the 16 sessions are distributed with the following emphasis: 4 sessions for working memory, 4 sessions for planning, 4 sessions for attention, and 4 sessions for inhibitory control and cognitive flexibility (the latter processes are integrated due to the lower number of available activities). Fig. 3 presents the selected digital activities from the NeuronUP platform, differentiating by type of activity (game, worksheet, and generator), the cognitive processes they train, and the session in which they are introduced.•**Control group**

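### The RM-ANOVA and the N of 58 treat the children as independent; if training sessions are shared, as seems likely but is not stated, session-group effects are counted as training-mode effects

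*Protocol article*

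**What the plan says.** **Allocation.** The Allocation section and Table 2 randomise individual children. The specifications table says that they come from two third-grade classes.

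**Delivery.** The Protocol design section describes a trial "involving two simultaneous groups: an experimental group undergoing computerized cognitive training" and an active control group doing paper-and-pencil training. For the computer arm, "The intervention will take place in the computer lab of the participating educational institution", twice a week for 16 sessions. The programme is common and timed: "Each session consists of 8 activities, each programmed for 5 min, for a total of 40 min per session". The paper arm follows the same structure, frequency and duration. Table 2 refers to the researchers who run the intervention in the plural, without giving their number or saying which arm each one serves.

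**Analysis.** Under Statistical analysis plan, pre-test and post-test form the within-subject factor and "the comparison between the experimental and control groups will serve as the between-subject factor". No session-group, leader or class term is named.

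**Sample size.** Table 1 lists "Effect size 0,75", "α confidence level 0,05" and "Sample power 0,8". The text adds: "This estimation suggests a group size of 29 children, resulting in a total sample size of 58 children". No ICC or design effect appears.

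**The concern.** Children who train together for eight weeks share a leader, a room, a time slot, interruptions and peers. Their post-test scores can then be correlated, and because each session group belongs to one arm, that correlation is nested within arm. It arises after randomisation, so random allocation does not remove it. Adjusting for school class does not remove it either, because a session group need not be a class.

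The child-level error term leaves this variation out. A calmer session group in one arm, or a more effective leader if leaders are tied to arm, would then appear as an effect of training mode. The trial could accept either alternative hypothesis for a reason unrelated to computer versus paper. If each arm is a single session group, arm and group coincide exactly and no later model can separate them. That is why the point matters before the first session.

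**Working it through.** **Are sessions shared?** The article does not say. One-to-one training would need 58 × 2 = 116 forty-minute sessions a week at one school. That makes shared sessions plausible, but it does not give the number of groups per arm.

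**Reproducing N.** Read 0.75 as a standardised mean difference and use a two-sided two-sample t-test at 0.05. Power is 0.787 with 28 per arm and 0.801 with 29, which gives 29 per arm and N = 58 exactly. Repeated-measures calculations with two groups, two measures and correlation 0.5 do not give 58: the totals are 14 (between) or 8 (interaction) at f = 0.75, and 44 or 18 at f = 0.375. The stated N is therefore matched by an ordinary comparison of independent children.

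**Assumptions for the error rate (not in the article).** Pre-post correlation r = 0.5, no true difference, a session-group effect on the post-test only, and the same ICC in both arms. With unit variances the change score has variance 2(1 − r) = 1, so the ICC of the change score equals that of the post-test.

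**False-positive rate.** With two time points, the group-by-time F is the square of the t statistic on change scores, with 56 df and critical value 2.003. With one group of 29 per arm:

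rate = 2 × P(T56 > 2.003 / √(1 + 29 × ICC/(1 − ICC)))

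At ICC 0.05, 29 × 0.05/0.95 = 1.526, √2.526 = 1.589 and 2.003/1.589 = 1.260, so the rate is 21.3%. The other rows come from simulation (20,000 trials per cell).

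| Session groups per arm | ICC 0.01 | ICC 0.02 | ICC 0.05 |
|---|---|---|---|
| 1 | 8.4% | 11.8% | 21.3% |
| 2 | 6.3% | 8.3% | 12.8% |
| 3 | 5.9% | 6.7% | 10.3% |
| 6 | 5.7% | 5.6% | 7.3% |

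A separate simulation of 60,000 trials gave 6.6%, 8.2% and 13.3% for two groups, 5.9%, 7.0% and 10.3% for three, and 5.7%, 6.2% and 8.0% for five. With no clustering the rate is 5%.

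**Sensitivity to r.** If the post-test ICC is 0.05 and r = 0.7, the change-score ICC is 0.05/(2 × 0.3) = 0.083. The one-group rate is then about 30%.

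**Precision at ICC 0.05.** With k groups per arm and unit SD, SE = √(2 × (0.95/29 + 0.05/k)), and power is approximately Φ(0.75/SE − 1.96).

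| k | SE | 95% half-width | Power at 0.75 |
|---|---|---|---|
| 1 | 0.407 | 0.80 | 45% |
| 3 | 0.314 | 0.62 | 66% |
| 6 | 0.287 | 0.56 | 74% |

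These powers treat the variance as known; the same approximation without clustering gives 81%. They describe a test that uses the right standard error, which with one group per arm cannot be estimated from the data.

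**The case against.** The strongest reply is that the premise is inferred. Session rosters and staffing are details that an article may leave to the full protocol, and their absence is no fault in itself. This stands, so the point is conditional. What the article does fix is the model and the sample size, and both assume independence.

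Four stronger readings are tempting and not supported:

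- A reader might take the phrase about simultaneous groups to mean that each arm trains as one group in one room. The specifications table calls the same design parallel, so the phrase may describe only the arms. The Limitations section names device availability as a constraint, which argues against 29 children in one lab session.
- A reader might infer that each arm has its own leader. Nothing says so. If leaders already serve both arms, a leader effect does not favour either mode, and only the session-group effect remains.
- A reader might quote 10–21% as the trial's false-positive rate. That range covers only one to three groups per arm at ICC 0.05. With five or six groups the rate is 7–8%, and at ICC 0.02 with two or more groups it is about 6–8%.
- A reader might say that the uncertainty exceeds the planned effect. The half-width of 0.80 belongs to one group per arm; with three it is 0.62.

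An equal ICC in both arms is also debatable. The computer tasks adapt to each child, which may weaken leader and peer influence in that arm.

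**Conclusion.** The point holds in conditional form. The plan commits to a model and a sample size with no allowance for session groups, while the described delivery makes shared sessions likely. If sessions are shared, the nominal 5% test runs at about 8–21% with one group per arm, 6–13% with two, 6–10% with three and 6–7% with six, over ICC 0.01 to 0.05. Power at ICC 0.05 falls below the stated 80% by an amount that depends mainly on the number of groups.

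The ICC, the number of groups, r = 0.5 and equal clustering in both arms are all assumptions, and the ranges are illustrations, not bounds. If children are trained individually and leaders are not tied to arm, the problem largely disappears and a sentence saying so is enough. If each arm is one session group, the analysis cannot repair it. The article does not show which case applies.

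**What to change.** 1. **Interventions.** State how sessions are grouped and led. If they are shared, have the same researchers lead computer and paper sessions in rotation, with time slots alternated, so that neither leader nor slot is tied to arm. Use at least two session groups per arm where rooms and devices allow.
2. **Statistical analysis plan.** Record each child's session group. Keep the planned RM-ANOVA and add a sensitivity analysis. One option is a session-group random effect with small-sample degrees of freedom. The other is the arm difference with its standard error multiplied by √(1 + (m − 1) × ICC), where m is the session-group size, over a range such as 0.01, 0.02 and 0.05. At m = 29 and ICC 0.05 the multiplier is √2.40 = 1.55. With one group per arm only the multiplier is available. With two per arm the random-effect test has about 4 − 2 = 2 degrees of freedom, so the multiplier will often be more informative. Use the result to qualify the conclusion. A pass/fail rule tied to an assumed ICC would be arbitrary.
3. **Table 1.** State that the 80% power assumes no session-group correlation.

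**Cost.** Some rescheduling, one recorded variable and one extra table, with no additional children or tests. Splitting an arm into more groups may add leader sessions. The sensitivity intervals will be wider, and the power statement becomes conditional.

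### Partial eta squared is unsigned, varies with each test's retest correlation and is not on the scale of the planning effect; a baseline-adjusted difference with a 95% interval would serve the hypotheses better

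*Protocol article*

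**What the plan says.** The Statistical analysis plan section of the protocol article sets a mixed repeated-measures ANOVA, with time (pre, post) within children and arm between children, followed by Bonferroni-corrected group comparisons. For the size of the effect it states: "Partial eta squared will be used to quantify effect size". No mean difference, standardised difference or confidence interval is named in the article.

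The Specific objectives and hypotheses section words the null as "There are no significant differences in executive functions between children receiving computerized cognitive training and those receiving paper-and-pencil cognitive training". It then gives two alternatives, one favouring computerised training and the other favouring paper-and-pencil training. They differ only in direction.

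The Sample size calculation section describes its planning effect as "based on previous studies that reported moderate to large effect sizes in similar research". Table 1 lists "Effect size 0,75", "α confidence level 0,05", "Sample power 0,8" and "Number of measures 2". It does not name the effect-size metric and lists no pre-post correlation. The result is: "This estimation suggests a group size of 29 children, resulting in a total sample size of 58 children".

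**The concern.** An effect measure should let the reader answer the trial's question and compare the answer with what the trial was built to detect. Here the question is directional, and the planning value appears to be a difference in SD units. Partial eta squared is a share of variance. It takes the same value whichever arm is ahead. In a pre-post design it also mixes the size of the between-arm difference with the stability of the test. The battery is varied (Tower of London, Digit Span, Corsi, Stroop, WCST, d2, Trail Making), so one common correlation is unlikely.

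What is at stake is interpretation. If the interaction is not significant, a partial eta squared alone does not tell the reader whether a difference of 0.75 SD, or a smaller one, has been excluded. If it is significant, the value cannot be set beside 0.75 without a correlation that the plan does not give.

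**Working it through.** **Inputs.** Effect 0.75, alpha 0.05, power 0.80, two groups, two measures, 29 per arm (Table 1). Pre-post correlation r: not in the document, so 0.3, 0.5, 0.7 and 0.8 are assumed. Equal SDs at pre-test and post-test are also assumed.

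**1. Reproduce N = 58.** Two-sided two-sample t test, standardised difference d = 0.75, non-central t:
- 28 per arm: power 0.787
- 29 per arm: power 0.801, so N = 58, an exact match

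Other readings tried do not reach 58. A one-sided t test needs 23 per arm. A repeated-measures F test with Cohen's f = 0.75 needs a total of 6 to 16 for r from 0 to 0.8. With f = 0.375 (that is, 0.75/2) it needs 10 to 30 for the interaction and 30 to 54 for the between-arm factor. The value 0.75 is therefore best read as a standardised mean difference.

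**2. Sign.** For a term with one numerator degree of freedom, partial eta squared = t²/(t² + 56). For t = +2.5 and t = −2.5 alike: 6.25/(6.25 + 56) = 0.100.

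**3. Dependence on r.** For the group-by-time term the standardised difference in change is d_c = 0.75/√(2(1 − r)). With equal arms, partial eta squared = d_c²/(d_c² + 4).

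| r (assumed) | d_c² | partial eta squared |
|---|---|---|
| 0.3 | 0.5625/1.4 = 0.402 | 0.402/4.402 = 0.091 |
| 0.5 | 0.5625/1.0 = 0.563 | 0.563/4.563 = 0.123 |
| 0.7 | 0.5625/0.6 = 0.938 | 0.938/4.938 = 0.190 |
| 0.8 | 0.5625/0.4 = 1.406 | 1.406/5.406 = 0.260 |

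The same true difference gives values almost threefold apart (0.260/0.091 = 2.9).

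In reverse, take an observed partial eta squared of 0.123 with 56 error degrees of freedom. Then t² = 0.123 × 56/0.877 = 7.85, and |d_c| = √(7.85 × 2/29) = 0.736. Multiplying by √(2(1 − r)) gives a between-arm difference of 0.87, 0.74, 0.57 or 0.47 SD at the four correlations, in either direction.

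**4. What a signed, adjusted estimate would show.** The approximate 95% half-width for a post-test difference adjusted for the pre-test score is t(0.975, 56) × √(2/29) × √(1 − r²) = 0.526 × √(1 − r²). This ignores the degree of freedom spent on the covariate and any chance pre-test imbalance.

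| r (assumed) | adjusted post-test difference | change-score difference, 0.526 × √(2(1 − r)) |
|---|---|---|
| 0.3 | ±0.50 SD | ±0.62 SD |
| 0.5 | ±0.46 SD | ±0.53 SD |
| 0.7 | ±0.38 SD | ±0.41 SD |
| 0.8 | ±0.32 SD | ±0.33 SD |

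An observed adjusted difference of zero would exclude 0.75 SD in either direction at every one of these correlations. A non-significant difference of 0.45 SD at r = 0.5 would not: its upper limit is 0.45 + 0.46 = 0.91 SD. The interval separates these two nulls directly.

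**The case against.** Partial eta squared is the usual companion of a repeated-measures ANOVA, and naming it contradicts nothing. A planning metric and a reporting metric may differ. The article condenses the plan, so other measures and intervals may be set out elsewhere. All of this stands, and it limits the point to an improvement on a stated choice.

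Several stronger readings are tempting, and the document does not support them:
- A reader might infer that the trial cannot say which arm is better. It can: the cell means and the Bonferroni-corrected comparisons show direction. Only the effect measure lacks it.
- A reader might infer that cognitive domains will be ranked by effect size, or that a non-significant result will be read as equal benefit. No section plans either.
- A reader might infer that outcomes moved to non-parametric tests will get no effect size. The sentence mainly governs the choice between parametric and non-parametric analysis, and a rank-based measure left unnamed in an article is missing detail, not an error.
- A reader might quote ±0.53 SD as the trial's precision. That is the unadjusted post-test interval, which equals the change-score interval only at r = 0.5.

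It can also be said that means, SDs and F allow d to be recovered. With full descriptive tables that is largely so, but then the plan should name the quantity that readers need.

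**Conclusion.** The point holds as a low-cost improvement. The effect measure that the article names is unsigned where the hypotheses are directional. For the group-by-time term it runs from about 0.09 to 0.26 for one and the same 0.75 SD difference, and it is not on the scale on which N = 58 reproduces. The range rests on assumed correlations of 0.3 to 0.8 and equal SDs. The scale mismatch rests on reading 0.75 as a standardised mean difference, which is inferred from the exact match with a two-sided t test. The sample size and the validity of the planned test are not affected.

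**What to change.** For every test, report the post-test difference (computer minus paper) adjusted for the pre-test score, from an ANCOVA or an equivalent model. Give it in test units and divided by the pre-test SD, each with a 95% confidence interval. Read the two directional alternatives, and any null result, from the sign and limits of that interval. State whether the intervals carry the Bonferroni correction. Keep partial eta squared as supplementary. Name the metric of the 0.75 in Table 1, so that estimate and planning value can be compared.

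The cost is one extra model per test. The planned RM-ANOVA does not supply this estimate, because its interaction gives a difference in change scores. No further data, children or visits are needed. The adjusted interval is also narrower than the change-score interval, for example ±0.46 against ±0.53 SD at an assumed correlation of 0.5.
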